# A three-arm, multicenter, open-label randomized controlled trial of hydroxychloroquine and low-dose prednisone to treat recurrent pregnancy loss in women with undifferentiated connective tissue diseases: protocol for the Immunosuppressant regimens for LIving FEtuses (ILIFE) trial

**DOI:** 10.1186/s13063-020-04716-1

**Published:** 2020-09-09

**Keywords:** Prednisone, Hydroxychloroquine, Recurrent pregnancy loss, Recurrent spontaneous abortion, Undifferentiated connective tissue disease, Randomized controlled trial

## Abstract

**Background:**

Undifferentiated connective tissue disease (UCTD) is known to induce adverse pregnancy outcomes and even recurrent spontaneous abortion (RSA) by placental vascular damage and inflammation activation. Anticoagulation can prevent pregnancy morbidities. However, it is unknown whether the addition of immune suppressants to anticoagulation can prevent spontaneous pregnancy loss in UCTD patients. The purpose of this study is to evaluate the efficacy of hydroxychloroquine (HCQ) and low-dose prednisone on recurrent pregnancy loss for women with UCTD.

**Methods:**

The Immunosuppressant for Living Fetuses (ILIFE) Trial is a three-arm, multicenter, open-label randomized controlled trial with the primary objective of comparing hydroxychloroquine combined with low-dose prednisone and anticoagulation with anticoagulation alone in treating UCTD women with recurrent spontaneous abortion. The third arm of using hydroxychloroquine combined with anticoagulant for secondary comparison. A total of 426 eligible patients will be randomly assigned to each of the three arms with a 1:1:1 allocation ratio. The primary outcome is the rate of live births. Secondary outcomes include adverse pregnancy outcomes and progression of UCTD.

**Discussion:**

This is the first multi-center, open-label, randomized controlled trial which evaluates the efficacy of immunosuppressant regimens on pregnancy outcomes and UCTD progression. It will provide evidence on whether the immunosuppressant ameliorates the pregnancy prognosis in UCTD patients with RSA and the progression into defined connective tissue disease.

**Trial registration:**

ClinicalTrials.gov NCT03671174. Registered on 14 September 2018.

## Background

Undifferentiated connective tissue disease (UCTD) is defined as at least one symptom or sign suggesting connective tissue diseases (CTDs) and with presence of at least one of auto-antibodies, while not fulfilling any classification criteria of a defined CTD [1, 2]. UCTD accounts for 20–52% of patients with CTDs and is characterized by varying symptom onset time and antibody profiles. UCTD is more common in women, with a male-to-female ratio ranging from 1:15 to 1:17, predominantly at the reproductive age with a prevalence of 2.5% in pregnant women [2–5]. UCTD may evolve into definite CTDs like systemic lupus erythematosus (SLE), systemic sclerosis, primary Sjögren’s syndrome, mixed connective tissue disease, systemic vasculitis, polymyositis, and rheumatoid arthritis [6].

UCTD is the most common rheumatic disease diagnosed during the first trimester of pregnancy and plays a potential causal role of autoimmune disorders in the occurrence of pregnancy complications [7]. Antinuclear antibodies and inflammation in UCTD may impair platelet activity, unbalance coagulation/anticoagulation, increase the risk of thrombosis, and cause collagen synthesis defect and endothelial dysfunction [8–10]. Therefore, it could increase uterine artery resistance, inhibit placenta development and remodeling, and thus increase the risk of preeclampsia, intrauterine growth retardation (IUGR), small for gestational age infant (SGA), and recurrent spontaneous abortion (RSA) [3, 11–14]. A multicenter retrospective cohort study showed that 21% of pregnancy resulted in miscarriages or stillbirths [15]. Spinillo found that women with UCTD had a higher rate (39.0%) of at least 1 spontaneous pregnancy loss than healthy controls with an odds ratio of 5.92 (95% CI, 2.1–17.8) [14]. Other studies reported that the prevalence of adverse pregnancy outcomes ranged from 27 to 30% in women with UCTD [13, 16].

In addition to adverse pregnancy outcomes, women with UCTD may experience a disease flare and even evolve into definite CTDs during the course of pregnancy and puerperium [17, 18]. The incidence of disease flare was about 24~32%, higher than the 11% in the non-pregnant patients [13, 16]. An average of 30% of UCTD women eventually develop a well-defined CTD [18–21], especially during pregnancy, and require treatments with steroids and immunosuppressants like hydroxychloroquine (HCQ).

There is no consensus or guideline about treatments for recurrent spontaneous abortion (RSA) in pregnant women with UCTD. UCTD shares similar pathogenesis of placental vascular thrombosis as systemic lupus erythematosus +/− antiphospholipid antibody syndrome (APS) for which low-dose aspirin and low molecular weight heparin (LMWH) are used to prevent fetal losses and improve pregnancy outcomes [22, 23]. Therefore, antiaggregation and anticoagulation were considered as a safe way of reducing the risk of miscarriages among women with UCTD [24, 25]. Despite low-dose aspirin and LMWH treatments, women who suffered from RSA with UCTD still suffered from pregnancy morbidity [24, 26].

Taking placental inflammation and imbalance of the immune system of UCTD into consideration, immunosuppression is hypothesized to be a potential rescue. Immunosuppression may also be beneficial in reducing disease recurrence and progression. Currently, commonly used immunosuppressant includes low-dose corticosteroids, HCQ, azathioprine, cyclosporin, and immunoglobulin [3]. In a guideline on prescribing drugs in pregnancy and breastfeeding, corticosteroids and HCQ are compatible with each trimester of pregnancy [level of evidence 1++, grade of recommendation A, strength of agreement 100%], and HCQ should be continued during pregnancy in women planning a pregnancy with rheumatic disease in need of treatment [27]. Corticosteroids and HCQ were used in nearly half of UCTD patients and considered as symptomatic treatment during the non-pregnancy period. But the treatment effect on pregnant women with UCTD was poorly studied and barely acknowledged, and most studies are small-scale observational studies. The studies of treatment in recurrent miscarriage, SLE, and APS showed that prednisone and HCQ could reduce the incidence of disease flares and obstetric complications. A low dose of corticosteroids was proved to inhibit T cells and natural killer (NK) cells, to improve the fertilization rate [28, 29], and to decelerate the progression into rheumatic diseases. Several studies showed that prednisolone of 5–20 mg per day can improve pregnancy outcomes [26, 30–33]. However, there still lacks a large clinical trial to identify optimal treatment. It was observed that HCQ was associated with delayed SLE onset in CTD [34], decrease the risk of disease flare in pregnant SLE patients [35–37], increase the live birth rate, reduce preterm delivery in antiphospholipid antibodies (aPL) positive patients [38], and prevent congenital heart block in neonates exposed to anti-SSA and anti-SSB antibodies [39]. It remains unknown whether HCQ could affect pregnancy outcomes of UCTD women. A study of 133 pregnancies of CTDs showed evidence for the safety of HCQ therapy during pregnancy but no differences in live birth rate [40]. A systemic review showed that HCQ does not appear to be associated with any increased risk of congenital defects, spontaneous abortions, fetal death, prematurity, or decreased numbers of live births in patients with autoimmune diseases [41]. Recently, data from 66 UCTD patients with RSA treated by hydroxychloroquine plus low-dose prednisone combined with anticoagulation in our center seemed promising. There were 66 successful pregnancies (the live birth rate 97.1%) and only 5 obstetric complications in 68 pregnancies. The impact on pregnancy outcome of UCTD is probably less severe than well-established rheumatic diseases; however, UCTD needs to be paid more attention to because of its high prevalence.

Given that RSA in UCTD patients is mediated by autoimmune factors and may be improved by the addition of immune suppressants to anticoagulation. The objective of the ILIFE trial is to assess the efficacy of low-dose corticosteroids and HCQ combined with anticoagulation in treating UCTD patients with recurrent pregnancy loss.

## Methods/design

### Study design

The ILIFE trial is a three-arm, multicenter, open-label, randomized controlled trial (RCT) to assess the efficacy of low-dose corticosteroids and HCQ combined with anticoagulation in treating UCTD women with recurrent pregnancy loss.

Patients will be enrolled at rheumatology outpatient clinics in six university-affiliated, tertiary hospitals in China, including Shanghai Renji Hospital, the First Affiliated Hospital of Anhui Medical University, China-Japan Union Hospital of Jilin University, the Affiliated Wuxi No.2 People’s Hospital of Nanjing Medical University, Jiangsu Province Hospital, and Xiangya Hospital of Central South University. The study design is presented in the flowchart in Fig. 1. Standard Protocol Items: Recommendations for Interventional Trials (SPIRIT) are provided as Additional file 1. This study was approved by institutional review boards (IRB) of study sites.

**Fig. 1 Fig1:**
[figure not shown]
Trial design schema

### Recruitment

The study population consists of UCTD women who had experienced at least two miscarriages and are trying to conceive. Rheumatologists in each study site will check inclusion and exclusion criteria of UCTD women. A research assistant will present the study information during recruitment. Eligible patients who provided informed consents will be enrolled in the trial.

The anticipated duration of recruitment is 2 years, and the duration of participation of each patient is about 2 years.

### Inclusion criteria

Women who meet the following inclusion criteria will be eligible to participate in the study:
At reproductive age (20–40 years old).Trying to conceive.Diagnosed with UCTD [2]: at least one symptoms or signs suggesting CTD and with at least one presence of auto-antibodies, including antinuclear antibody (ANA), anti-extractable nuclear antigen (ENA) antibodies, anti-double-stranded DNA (ds-DNA) antibody, aPL, and anti-cyclic citrullinated peptide (CCP) antibody, while not fulfilling any classification criteria of a defined CTD.Diagnosed with RSA [42]: two or more failed pregnancies of unknown origin in all trimesters.Providing written informed consent.

### Exclusion criteria

Women who meet any of the following criteria will be excluded from the study:
Any known etiology of previous pregnancy loss:Diagnosis of antiphospholipid antibody syndrome.Known paternal, maternal, or embryo chromosome abnormality.Maternal endocrine dysfunction: corpus luteal insufficiency, polycystic ovarian syndrome, premature ovarian failure (follicle-stimulating hormone, FSH ≥ 20 U/L in follicular phase), hyperprolactinemia, thyroid disease, diabetes mellitus, and other hypothalamic–pituitary–adrenal axis abnormality.Maternal anatomical abnormality: uterine malformation (using Thessaloniki ESHRE/ESGE consensus criteria, gynecological examination, ultrasound results, and opinions of obstetricians and gynecologists), Asherman syndrome, cervical incompetence, and uterine fibrosis more than 5 cm (including submucosal and/or intramural).Vaginal infection.Any known severe cardiac, hepatic, renal, hematological, or endocrinal diseases:Alanine transaminase (ALT) or aspartate transaminase (AST) more than twice the upper limit of normal.Clearance of creatinine less than 30 mL/min.Leucocytes less than 2.5 × 10^9^/L, hemoglobin less than 85 g/L, or platelet less than 50~10^9^/L.Any active infection:Active viral hepatitis including hepatitis B virus (HBV), hepatitis C virus (HCV).Active infection including varicella-zoster virus (VZV), human immunodeficiency virus (HIV), syphilis, or tuberculosis.Allergic to prednisone, hydroxychloroquine, LMWH, or aspirin.Disease history as follows:Past history of digestive ulcers or upper gastrointestinal hemorrhage.Past history of malignancy.Past history of epilepsia or psychotic disorders.Women using assisted conception.Women unable to consent.

### Randomization and blinding

The primary objective of this trial is to investigate the superiority of low-dose corticosteroids and HCQ combined with anticoagulation compared with anti-coagulant only in UCTD women with RSA. A third arm of using hydroxychloroquine combined with anticoagulant for a secondary comparison only. It is an open-label trial, but data analysts will be blinded. After obtaining the written informed consent, eligible patients will be randomized to one of the three treatment arms with a ratio of 1:1:1 stratified by site. Randomized numbers will be generated through SAS software at the trial methods center located in Shanghai Renji Hospital. A specially designed sealed opaque two-couplet random allocation envelope will be used for the randomization and allocation. The first couplet is to collect the enroll information and the second couplet is to show the allocation information. The content of the first couplet can be completely copied to the second couplet. Each time a new patient is enrolled in the study, a new envelope will be opened in order. Once the envelope is opened, it cannot be resealed.

### Treatments

Included patients are randomized to three treatment groups: (1) low-dose prednisone (10 mg once daily orally), HCQ (the maximal tolerance dose ranges from 100 to 400 mg daily orally), and anticoagulants using low-dose aspirin (50 mg once daily orally) and subcutaneously administered LMWH once daily with preventive dose (enoxaparin 40 mg or dalteparin 5000 IU or nadroparin calcium 4100 U); (2) HCQ (the maximal tolerance dose ranges from 100 to 400 mg daily orally), and the same anticoagulant treatments as in the first group; and (3) the anticoagulant treatments only. Treatments are initiated before conception (recommended 3–6 months) and stopped at 6 weeks post-gestation or miscarriage or after 1 year of treatment in the absence of pregnancy. Supplements such as folic acid, calcium tablet, and vitamins are allowed throughout pregnancy.

### Assessments and data collection

The assessments will be conducted at the screening and preparation phases and then routinely throughout the trial. The screening phase will last for 4 weeks. General profiles including age, height, weight, ethnicity, occupation, obstetric and rheumatology histories, medication uses, allergy, and antecedents will be recorded during the screening phase. Following the screening phase is the 1-year pre-conception phase. If participants are not pregnant within 1 year, the treatment and their participation will be terminated. Once pregnancy is confirmed, the pregnancy assessments will start and the index time is set to week 0. Pregnant women will be followed once every 4 weeks in the next 42 weeks gestation period. The last visit will be conducted at 6 weeks after delivery. The assessment will be terminated when spontaneous pregnancy loss or childbirth takes place. Children’s observations will last for 1 year after the end of the study, including vision, hearing, and growth parameters. The schedules for assessments and data collection are showed in Fig. 2. Data will be collected in paper case report forms (CRFs) stored at a secure place and double entered into the electronic trial database.

**Fig. 2 Fig2:**
[figure not shown]
SPIRIT figure: time schedule of enrollment, interventions, and assessments. An asterisk denotes blood count, biochemistry, autoimmune profile, and coagulation profile

### Outcome measures

#### Primary outcome

The primary outcome is the rate of live births after at least 26 completed weeks of gestation.

### Sample size

There is very limited evidence on the spontaneous pregnancy loss in pregnancies of women with UCTD and the reported risk rates for RSA varied substantially across studies. The live birth rate of a randomized trial enrolling 364 women with a history of unexplained recurrent miscarriage was 69.1% in the group receiving aspirin plus nadroparin [43]. In another cohort study of women with positive aPL, HCQ can improve the live birth rate from 57 to 67% [38]. A double-blind placebo randomized control trial involving 160 patients with unexplained recurrent miscarriage showed that the addition of prednisolone to heparin and aspirin might be beneficial, with 70.3% of women in the prednisolone group having successful pregnancy outcome versus 9.2% in the placebo group [30]. Data from 68 pregnancies in our department showed that the live birth rate was 97.1% in UCTD women with RSA treated by hydroxychloroquine plus low-dose prednisone combined with anticoagulation.

Our primary comparison is between the combined use of prednisone, HCQ, and anticoagulant with the anticoagulant only. Based on our pilot and limited published data, we hypothesize that the proportion of live birth rates with the treatment strategy using prednisone, HCQ, aspirin, and LMWH is 85% vs 70% for anticoagulant only. We need to enroll 363 women (121 in each group and for the third arm as well) to allow us to detect the difference in spontaneous pregnancy loss between the treatment groups with a power of 0.8 at a two-sided *P* value of 0.05. Since not all women would get pregnant during the trial, we planned to include about 426 participants (142 in each group) on the assumption of 90% of the pregnant rate within 1 year and 5% loss to follow-up [44].

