### Data analysis

The primary analysis is to compare the rate of live births after at least 26 completed weeks of gestation between the combined use of prednisone, HCQ, and anticoagulant with the anticoagulant only. All data will be analyzed according to the intention-to-treat approach in which all randomized patients are included and supplemented by per-protocol analysis. For categorical data, frequencies and percentages will be presented. Continuous data will be presented as the mean and standard deviation or median and interquartile range. Comparison between groups will be performed using the independent sample *t* test, Pearson’s *χ*^2^ test, or Fisher’s exact test as appropriate. The primary outcome will be summarized as the proportion of live birth in each group. The absolute differences and relative risks with 95% confidence intervals will be described for the primary and secondary outcomes. The relative risks will be adjusted for age and number of previous miscarriages.

The trial has a single primary endpoint, i.e. rate of live births after at least 26 completed weeks of gestation between the combined use of prednisone, HCQ and anticoagulant with the anticoagulant only. All secondary comparisons, including comparisons to the third treatment arm (HCQ and anticoagulant) will be performed to further inform the primary endpoint and will be interpreted on this basis.

A sensitivity analysis using multiple imputations will assess the robustness of the results to variation in the missing data assumptions. Subgroup analysis will be conducted according to the number of previous miscarriages (2 or ≥ 3). Two-tailed significance tests will be performed at the 5% significance level, without adjustment for multiple testing.

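### The 80% power belongs to pregnant, followed-up women; on the all-randomised primary analysis the plan's own assumptions give about 63–70%

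*Protocol article*

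**What the plan says.** Three sections of the protocol article bear on this.

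- **Sample size.** The planning rates are live birth rates: "using prednisone, HCQ, aspirin, and LMWH is 85% vs 70% for anticoagulant only". The section asks for 121 women per arm "to allow us to detect the difference in spontaneous pregnancy loss between the treatment groups with a power of 0.8" at a two-sided 5% level. It then raises the number because some women will not become pregnant: "we planned to include about 426 participants (142 in each group) on the assumption of 90% of the pregnant rate within 1 year", together with 5% loss to follow-up. The centre's own figure behind the hypothesis is counted in pregnancies: "Data from 68 pregnancies in our department showed that the live birth rate was 97.1" per cent.
- **Data analysis.** The primary comparison is live birth after at least 26 completed weeks, triple therapy against anticoagulation alone. The population is every woman randomised: "All data will be analyzed according to the intention-to-treat approach in which all randomized patients are included". Per-protocol analysis is a supplement, and multiple imputation is a sensitivity analysis.
- **Assessments and data collection.** Women enter while trying to conceive and have a one-year pre-conception phase. "If participants are not pregnant within 1 year, the treatment and their participation will be terminated".

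No section restricts the primary outcome to women who become pregnant.

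**The concern.** Inflating a sample size makes up for women who leave the denominator. It does not make up for women who stay in it as failures, because they also shrink the difference between arms. The Sample size section treats women who do not conceive as drop-outs; the Data analysis section keeps them in. The stated power and the stated primary analysis therefore refer to different populations.

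Two things are at stake. A null result would be read as coming from a trial with 80% power when the planned test has clearly less. And with two denominators in play for a single primary endpoint in an open-label trial, there would be pressure to move to the per-pregnancy one once results are known.

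The power sentence adds to the ambiguity by naming spontaneous pregnancy loss instead of live birth. A woman who never conceives has neither, so the two endpoints treat her differently.

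**Working it through.** **Inputs**

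- Live birth 85% vs 70%; power 0.80; two-sided 0.05; 90% pregnant within one year; 5% lost (Sample size).
- 1:1 allocation for the primary comparison (Randomization and blinding).
- All randomised women analysed (Data analysis).
- Assumed here: the 90% and 5% apply equally in both arms, and a woman who does not conceive counts as no live birth.

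**Step 1. Reproduce the plan's figures.** Pooled two-proportion formula, no continuity correction, with p̄ the mean of p1 and p2:

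n = [1.960·√(2p̄(1−p̄)) + 0.842·√(p1(1−p1) + p2(1−p2))]² / (p1−p2)²

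With p1 = 0.85, p2 = 0.70, p̄ = 0.775:

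n = [1.960 × 0.5906 + 0.842 × 0.5809]² / 0.15² = 120.5, so 121 per arm (power 80.2%).

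Inflation: 121 / (0.90 × 0.95) = 141.5, so 142 per arm and 426 in total. Both figures match. Read backwards, 142 × 0.90 × 0.95 = 121.4 pregnant, followed women per arm.

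**Step 2. Rates on the all-randomised scale**

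- Triple therapy: 0.90 × 85% = 76.5%.
- Anticoagulant only: 0.90 × 70% = 63.0%.
- Difference: 13.5 points, not 15.
- If lost women also count as no live birth, multiply by 0.95: 72.7% vs 59.9%, a difference of 12.8 points.

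**Step 3. Power**

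Power = Φ{[|p1−p2|·√n − 1.960·√(2p̄(1−p̄))] / √(p1(1−p1) + p2(1−p2))}

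For 142 per arm at 76.5% vs 63.0%: Φ{(1.6087 − 1.2732) / 0.6426} = Φ(0.522) = 69.9%.

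| Handling of the 5% lost | n per arm | Rates | Power (formula) | Exact, Pearson χ² | Exact, Fisher |
|---|---|---|---|---|---|
| No losses | 142 | 76.5% vs 63.0% | 69.9% | 70.0% | 65.6% |
| Lost women left out | 135 | 76.5% vs 63.0% | 67.7% | 68.2% | 63.4% |
| Lost women counted as no live birth | 142 | 72.7% vs 59.9% | 62.9% | 63.4% | 58.6% |

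**Step 4. What 80% power would take**

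- At 76.5% vs 63.0%: n = 180.6, so 181 analysed per arm. Allowing for 5% left out, 181 / 0.95 = 190.5, so 191 per arm and 573 in total.
- At 72.7% vs 59.9%: n = 212.2, so 213 per arm and 639 in total.
- With 142 per arm and a control rate of 63.0%, the rate detectable with 80% power is 78.1%, a difference of 15.1 points. Per pregnancy that is 78.1 / 0.90 = 86.8% vs 70%.

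**Step 5. Sensitivity to the conception rate (142 per arm, no losses)**

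- 80% conceiving in both arms: 68.0% vs 56.0%, power about 55%.
- Unequal conception, triple therapy first: 91% vs 89% gives 79%; 92% vs 88% gives 87%; 89% vs 91% gives 59%.

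**The case against.** The strongest reply is that the article never says how a woman who does not conceive is coded. The primary outcome has no stated denominator, her participation ends at one year, and the sample-size text points to a per-pregnancy rate. On that view only an undefined denominator is certain, and the power loss follows from one way of resolving it. This has limited force. The article does say that all randomised women are included, and a woman known not to have conceived has a known outcome; she is not missing. Nor can 85% and 70% be read as rates per randomised woman. Power would then be 84–86% (135 or 142 per arm), but the inflation for non-pregnancy would make no sense.

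Other points stand as qualifications:

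- The 63% figure needs a further rule, that lost women count as failures, which the article does not state. Without it the range is 68–70%.
- Equal conception across arms is an assumption, and power is sensitive to it, as Step 5 shows. The article gives a single 90%, so equality is the fair default.
- The arithmetic for 121 and 142 is right; the fault is the mismatch of populations.
- The mismatch neither biases the estimate nor raises the type I error.
- The pregnancy-loss wording is minor, since the sentence before it gives the rates as live birth.

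Analysing only pregnant women would restore the stated power, but not cleanly. Treatment starts before conception and conception rate is itself a secondary outcome, so that comparison conditions on an event after randomisation that treatment could affect.

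**Conclusion.** The concern holds. The sample-size section and the primary analysis cannot both stand as written: about 121 pregnant, followed women per arm carry the 80% power, while the primary test includes all 142 randomised. On the plan's own rates, power is about 70% with complete follow-up, 68% with the 5% lost left out and 63% with them counted as failures. The type II error is thus 30–37%, not 20%. These figures assume 90% conception in both arms and no live birth for women who do not conceive. An analysis plan cannot reconcile the two statements: it must give up either the all-randomised analysis or the 80%. Because this concerns the stated power and denominator of the single primary endpoint, it must be corrected.

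**What to change.** Keep live birth after at least 26 completed weeks among all randomised women as the primary outcome, and amend the text as follows:

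1. State the denominator in the primary-outcome section, with women who do not conceive within one year counted as having no live birth, and state how women lost to follow-up are counted.
2. Give the planning rates as 76.5% vs 63.0%, with equal 90% conception in both arms as an explicit assumption.
3. Give the power of 142 per arm as about 70% (63–68% allowing for 5% loss, depending on how lost women are counted), or state the difference detectable with 80% power, about 15 points on the all-randomised scale.
4. Name live birth, not pregnancy loss, in the power sentence.
5. Label live birth per pregnancy as a supplementary analysis.

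The cost is rewording and a less favourable power statement; no extra patients are needed. If the sponsor wants to keep 80% power for the all-randomised analysis, the alternative is to re-size to 573 women in total with lost women left out, or 639 with them counted as failures, against 426 now.
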